### Randomization procedure

After providing informed consent and baseline measurement, randomization will be performed by an independent person with the use of a computer generated randomization list using block randomization with random block sizes between 3 and 10. This sequence is kept hidden from all involved researchers. It can be expected, that patients referred by a GP and patients referred by a sports physician are different in terms of BMI and activity level. These have both been described as possible risk factors for plantar fasciopathy and therefore might influence treatment response [8]. For this reason the randomization will be stratified for type of referral (GP or sports physician). As a consequence patients from both populations will be equally distributed across the three treatment arms.

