### Follow-up measurements

The 2, 4 and 6 week questionnaires will include questions on recovery on a 7-point Likert scale [38], pain at rest and during activity (NRS) and foot function (FFI). The questionnaires at 12 and 26 weeks will include these questions as well and will additionally include questions on general health (SF12), quality of life (EuroQol), direct cost (medical costs: health care visits, medication, medical devices), indirect cost (absence from work, inability to work) and current activity level. The patients randomized to the two podiatrist groups will also complete questions on patient satisfaction and compliance to treatment in the questionnaires at 12 and 26 weeks. In the 26 week questionnaire we will additionally ask all patients allocated to podiatric treatment to report their expectation regarding the type of insole they received, in order to assess the successfulness of blinding.

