### Data analysis

Differences between the intervention groups will be analyzed following the intention-to-treat principle. Linear regression techniques for repeated measurements will be used to compare pain severity between the intervention group and control groups, which take the correlation of multiple measurements within one patient into account. A Bonferroni correction will be performed for the secondary comparisons to the usual care group. The analysis will be adjusted for potential confounders (at least including age, gender, BMI and activity level).

Recovery, pain scores and function will be analyzed using regression techniques for repeated measures using generalized mixed models.

Mean direct, indirect and total costs will be estimated and compared between the three study groups. Because costs will not be normally distributed, 95 % confidence intervals for the differences in mean costs will be obtained by bias corrected and accelerated bootstrapping (2000 replications). Differences in costs and differences in recovery will be included in a cost-effectiveness ratio, which estimates the additional costs to completely recover one patient.

Confidence intervals for the cost-effectiveness ratio will be calculated with bootstrapping, using the bias-corrected percentile method with 5000 replications. An incremental cost-effectiveness ratio will be estimated of the incremental costs to recover one patient. Uncertainty of this ratio will be evaluated by presenting a cost-effectiveness plane and sensitivity analyses will be performed to check the robustness of the results. An acceptability curve will also be presented.

Pre-defined subgroup analysis will be performed in patients with a long (>12 months) and short (<12 months) duration of the complaints at baseline, in patients with a low, moderate or high total activity score derived from the SQUASH questionnaire (in tertiles), in patients recruited in general practice and by sports physicians and in patients where the podiatrist agrees with the indication for orthotic insoles and in patients where the podiatrist does not.

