We will include patients from both general practice and sport medicine clinics. Previous studies have suggested possible subgroups of patients, which might be represented by the two different recruitment settings. For example, patients recruited in general practice are more likely to be middle-aged with perhaps higher mean BMI’s, whereas patients recruited by sports physicians are probably more physically active compared to those in general practice. By performing a stratified randomization for type of referral we will be able to analyze the possible difference in effectiveness of insoles in subgroup analysis.

Our sample size calculation is based on the data from Landorf et al. [18] This trial is to tour knowledge the only trial that has compared a custom made insole to a sham insole. The pain score in this trial was derived from the Foot Health Status Questionnaire, which is a pain score with a scale from 0 to 100. The primary outcome of the present study is pain severity measured on a 0–10 point NRS-scale. In order to determine our sample size, we have rescaled the pain severity outcomes for application on the 0–10 NRS.

The strength of this study is that we will perform a trial in which we will compare custom made insoles, a preferred treatment in patients with plantar fasciopathy, to a placebo treatment and usual care. The results will contribute to clinical decision making in primary health care when it comes to plantar fasciopathy and will additionally provide information on the cost-effectiveness of podiatric care including orthotic insoles.

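### The primary model does not commit to including referral type, the factor on which randomization is stratified; the cost is probably small and conservative

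*Protocol article*

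**What the plan says.** The Randomization procedure section expects that "patients referred by a GP and patients referred by a sports physician are different in terms of BMI and activity level". Of those two characteristics it says: "These have both been described as possible risk factors for plantar fasciopathy and therefore might influence treatment response". It then concludes: "For this reason the randomization will be stratified for type of referral (GP or sports physician".

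The Data analysis section describes the primary model: "Linear regression techniques for repeated measurements will be used to compare pain severity between the intervention group and control groups". On covariates it says: "The analysis will be adjusted for potential confounders (at least including age, gender, BMI and activity level". Referral type is not named there.

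Referral type has one stated use in the analysis, as a subgroup factor. The Data analysis section plans a subgroup analysis "in patients recruited in general practice and by sports physicians", and the Discussion gives the same purpose: "By performing a stratified randomization for type of referral we will be able to analyze the possible difference in effectiveness of insoles in subgroup analysis".

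Activity level is collected at baseline with the SQUASH and Tegner questionnaires (Baseline measurement). The 12- and 26-week questionnaires also ask about "current activity level" (Follow-up measurements). The covariate sentence does not say which measurement it means.

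**The concern.** Stratified randomization makes the arms alike on the stratification factor. The treatment estimate therefore varies less from one randomization to the next than it would under simple randomization. A model that contains the factor reflects this in its standard error. A model without it leaves the variance between strata in the residual, so the reported standard error is larger than the true one. Confidence intervals are then slightly too wide, and the test rejects slightly less often than its nominal level.

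The article restricts randomization on one factor only and names four covariates, and that factor is not one of them. At stake is a modest amount of precision in the primary comparison, and a clear link between how patients were allocated and how they are analysed. The validity of the treatment estimate is not at stake.

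**Working it through.** **The plan's own figure.** The Sample size section gives an effect size of 0.5, 80% power and two-sided alpha of 0.05. Then n per group = 2 × (1.960 + 0.842)² / 0.5² = 62.8, which rounds up to 63. The stated 63 reproduces. With the stated difference of 10.5 and SD of 21.5 entered directly, the standard error is 21.5 × √(2/63) = 3.83, the ratio 10.5/3.83 is 2.741, and power is Φ(2.741 − 1.960) = 0.783. That is the starting point for the power figures below.

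**Assumption.** Let R² be the share of outcome variance that referral type explains after the named covariates. The article gives no value, so a range of 0.01 to 0.10 is used. The SD of 21.5 is taken as the residual SD when referral type is omitted. The arms are taken as balanced on referral type, which stratified blocks should achieve closely.

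**Formulas** (large sample), with k = √(1 − R²):
- overstatement of the standard error when referral type is omitted: 1/k − 1
- true two-sided error of a nominal 5% test: 2 × [1 − Φ(1.960/k)]
- power, referral type omitted: 1 − Φ((1.960 − 2.741)/k)
- power, referral type included: Φ(2.741/k − 1.960)

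| Assumed R² | SE overstated by | True type I error | Power, omitted | Power, included | Difference |
|---|---|---|---|---|---|
| 0.01 | 0.5% | 0.049 | 0.784 | 0.787 | 0.003 |
| 0.02 | 1.0% | 0.048 | 0.785 | 0.791 | 0.006 |
| 0.05 | 2.6% | 0.044 | 0.789 | 0.803 | 0.014 |
| 0.10 | 5.4% | 0.039 | 0.795 | 0.824 | 0.029 |

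Example for R² = 0.05: k = √0.95 = 0.975. Then 1/k = 1.026, the true error is 2 × [1 − Φ(2.011)] = 0.044, power when omitted is 1 − Φ(−0.781/0.975) = 0.789, and power when included is Φ(2.741/0.975 − 1.960) = 0.803.

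**Where in the range.** Referral type was chosen because the two groups should differ in BMI and activity level. Both are already in the model, so what referral type adds beyond them is probably towards the low end.

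The standard-error and type I error columns do not depend on the group size, so they carry over to the comparison with usual care. Nothing here changes the planned sample size.

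**The case against.** The case on the other side is strong on size. The covariate list is a minimum, so referral type may be added without departing from the plan. Referral type was picked for what it stands for. The Discussion describes the two settings by age, BMI and physical activity, and all three are named covariates. Balance between arms is kept whatever model is fitted, and the subgroup analysis by setting is pre-defined. All of this stands, and it is why the cost is put as small and conservative. It does not remove the point: permission to add the factor is not a commitment, and a subgroup analysis does not take the between-setting variance out of the primary standard error.

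A reader might infer four stronger things that the article does not support:

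- *The analysis excludes referral type, so its p-values and intervals are wrong.* The text excludes nothing. If the factor is left out, the error is slight and on the cautious side.
- *The benefit of stratifying is lost.* The balance and the subgroup purpose both remain.
- *The model will adjust for activity measured after treatment, and so remove part of the effect.* The wording leaves the time point open, but activity level is listed beside age, gender and BMI, all baseline items. Nothing says that the follow-up measurement enters the model.
- *The open list will be filled in after seeing results.* The article says nothing of the kind, and a final covariate list is commonly left to an analysis plan. In an illustrative simulation (126 patients, four fixed and five optional covariates), always taking the most favourable of 32 models raised a 5% error to about 13% or 28%, for assumed covariate–outcome correlations of 0.2 or 0.3. That is a worst case under assumed conduct, not an estimate for this trial.

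The last two are reasons to word the fix tightly. They are not separate faults.

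**Conclusion.** The point holds in a limited form. The article stratifies on referral type and does not commit the primary model to it. If the factor is left out, the standard error is overstated by about 0.5% to 5%, the true type I error is about 0.049 to 0.039 against a nominal 0.05, and about 0 to 3 percentage points of power are forgone.

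These figures rest on an assumed residual R² of 0.01 to 0.10, close balance on referral type within blocks, and large-sample formulas. The low end is the more plausible, because BMI and activity level are already adjusted for. This is a nearly free improvement and does not threaten the trial's conclusions.

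**What to change.** Rewrite the covariate sentence in the Data analysis section so that the primary repeated-measures model is adjusted for referral type (the stratification factor), age, gender, BMI and activity level measured at baseline. State that this set is fixed before unblinding and that any other covariate set is reported only as a sensitivity analysis. Keep the subgroup analysis by recruitment setting as it is. If a separate analysis plan exists, it should carry the same list.

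The cost is one sentence and one degree of freedom. Referral type is known for every patient at randomization and activity level is already collected at baseline, so neither data collection nor the sample size of 185 changes.

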## Background

Plantar fasciopathy is a common cause of foot pain in both primary and secondary care. Plantar fasciopathy was formerly known as plantar fasciitis in literature. It typically affects middle aged or older women (40–60 years), with being overweight as a risk factor [1–3]. Besides this, plantar fasciopathy is also commonly seen in highly physically active people; plantar fasciopathy accounts for 8–10 % of all running related injuries [4]. Plantar fasciopathy accounts for approximately 11 to 15 % of all foot symptoms requiring professional care among adults and it has been estimated that a general practitioner (GP), with an average size practice, diagnoses around eight new patients each year [5, 6].

The etiology of plantar fasciopathy is poorly understood and is probably multifactorial [7, 8]. Histopathology studies have indicated that fasciopathy of the plantar fascia might be a possible cause of pain [9, 10]. Repetitive microtrauma and inflammation have been suggested as possible etiologic mechanisms, however these conclusions are mostly based on clinical experience and there is little evidence from research [11–13].

Plantar fasciopathy is characterized by pain over the anteromedial aspect of the inferior heel and the pain tends to increase after periods of inactivity or during weight bearing activities. The diagnosis can be made primarily based on symptoms and physical examination [7]. Patients often report low quality of life and reduced participation as their heel pain prevents them from performing simple every day activities [14, 15]. The clinical course of plantar fasciopathy is considered favorable as 80 % of patients will have a complete resolution of symptoms within 12 months [7]. Despite the favorable clinical course on the long term, many patients do expect and hope for short term pain relief and often multiple treatments are applied during the course of their complaints [7, 16].

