The most commonly prescribed treatments include footwear modification, taping, stretching exercises, anti-inflammatory agents, Extra Corporal shock wave therapy (ESWT) and cortisone injections [7, 12]. Reviews conclude that most of these treatments have a role in the management of plantar fasciopathy although at different time points in the clinical course [7, 11–13, 17]. Despite the use of many different treatment strategies in plantar fasciopathy, there is insufficient evidence for the effectiveness of these treatments provided by high quality randomized controlled trials [12, 13, 18, 19].

It has therefore been suggested that treatment options should be offered to the patient in sequence, either based on objective patient criteria or based on the preference of the patient [12]. Different combinations of conservative treatments successfully manage 85–90 % of the cases of plantar fasciopathy [16]. Orthotic devices seem to be a frequently applied treatment option, despite a lack of evidence on the effectiveness [6, 16]. A clinical practice guideline from the American College of Foot and Ankle Surgeons recommends anti-inflammatory drugs (NSAIDs), stretching and prefabricated orthotics as the initial steps in the conservative treatment of plantar heel pain and prescription orthotic devices as a secondary treatment option [6]. Orthotic devices include a low risk intervention, they are relatively painless compared to other treatments, such as shock wave therapy or cortisone injections, and they have a working mechanism that influences on what are thought to be important biomechanical factors in the etiology of plantar fasciopathy. There are different theoretical models on the potential working mechanism of orthotic devices [20]. The most common theory is that orthotic devices optimize the biomechanical loading of the foot, specifically to decrease excessive pronation, to off-load the plantar fascia at its origin and to recreate the heel pad [21].

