### Patient selection

Patients with plantar fasciopathy, characterized as pain at the medial hind foot, presenting themselves to a GP or sports physician, aged between 18 and 65 years and a minimal pain duration of 2 weeks are eligible for participation.

Participants will be excluded if they have recurrent complaints of plantar fasciopathy for more than 2 years, complaints caused by trauma, earlier treatment for plantar fasciopathy by a podiatrist or treatment with orthotics, suspected (by the GP or sports physician) (osteo)arthritis in the subtalar or talonavicular joint, suspected tarsal tunnel syndrome, suspected stress fractures, infections or tumors in the painful foot or presence of systemic diseases (such as Bechterew’s disease, psoriasis or multiple sclerosis). Patients who have no sufficient understanding of the Dutch language will also be excluded, since they will not be able to complete the questionnaires.

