### Baseline measurement

The baseline questionnaire will include questions on demographics (age, gender, BMI, education level, work and comorbidities), duration of pain, work activity (type, magnitude and load), sports activities (including the validated questionnaires SQUASH and Tegner) [30, 31], general health (SF12) [32], quality of life (EuroQol 5 dimensions) [33], neuropathic pain (DN4) [34], function (Foot Function Index (FFI)) [35], disability (Manchester-Foot Pain and Disability Index questionnaire (MPDI) [36], pain at rest and during activity (11-point NRS-scale) [37], incidence of falling, type of shoes and previously received medical care.

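### Baseline duration of complaints is not among the named adjustment covariates, so a modest and nearly free gain in power is left to later choice

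*Protocol article*

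**What the plan says.** All places are in the protocol article.

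- **Data analysis**, on covariates: "The analysis will be adjusted for potential confounders (at least including age, gender, BMI and activity level". This follows the description of the repeated-measures regression for pain severity. The next paragraph, on recovery, pain scores and function, specifies mixed models and names no covariates.
- **Baseline measurement** lists "duration of pain, work activity (type, magnitude and load" among the baseline items. Under Recruitment of study population, randomization follows completion of that questionnaire.
- **Patient selection** admits patients with "a minimal pain duration of 2 weeks" and excludes recurrent complaints lasting more than 2 years.
- **Data analysis**, on subgroups, contrasts patients with "long (>12 months) and short (<12 months) duration of the complaints at baseline". It is the first subgroup listed.
- **Randomization procedure** stratifies by type of referral only. The reason given is that the two referral populations may differ in BMI and activity level.
- **Background** says that "80 % of patients will have a complete resolution of symptoms within 12 months", and that "most of these treatments have a role in the management of plantar fasciopathy although at different time points in the clinical course".

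**The concern.** Patients enter at very different points of a condition that usually resolves with time. Where a patient stands in that course is a plausible predictor of pain at 12 weeks and of recovery. The Discussion itself allows that improvement in both arms of the earlier trial may reflect natural course. Duration is already collected, precedes randomization and is used for a subgroup analysis. The named covariates are instead age, gender, BMI and activity level, and the design does not balance duration.

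Two things are at stake, both limited. If duration does predict outcome, leaving it out keeps avoidable variance in the error term. And an open-ended list means that adding it, or not, may be decided after outcomes have been seen.

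**Working it through.** **1. The plan's own figure.** With effect size 0.5, two-sided alpha 0.05 and 80% power, n per arm = 2(1.960 + 0.842)² / 0.5² = 62.8, so 63, as the Sample size section states. The unrounded inputs give 10.5/21.5 = 0.488 and n = 65.8, so 66. At 63 per arm with 0.488, power is 78.3% (normal approximation). The calculation takes no credit for covariates.

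**2. Patients left after loss.** 69 × 0.90 = 62.1, so 62 per arm for custom versus placebo.

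**3. Pain, with duration added.** Let R² be the share of the remaining outcome variance that duration explains after the named covariates. The documents give no value, so 3 to 10% is an assumed range. The residual SD becomes 21.5 × √(1 − R²), and the standardized effect 0.488 / √(1 − R²). Two-sample t-test, 62 per arm, two-sided 0.05:

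| R² (assumed) | Standardized effect | Power | Equivalent gain in patients, 1/(1 − R²) − 1 |
|---|---|---|---|
| 0 | 0.488 | 77.0% | 0% |
| 0.03 | 0.496 | 78.2% | 3% |
| 0.05 | 0.501 | 79.0% | 5% |
| 0.10 | 0.515 | 81.2% | 11% |

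Over a wider range, at 63 per arm by the normal approximation, power is 78.7% for a partial correlation of 0.1, 79.9% for 0.2, 81.9% for 0.3, 84.9% for 0.4 and 88.6% for 0.5. The standard error falls by 0.5%, 2.0%, 4.6%, 8.3% and 13.4%.

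**4. Recovery.** A logistic model at a single time point was simulated with 63 per arm and 1,500 replicates per row. All inputs are assumed: treatment odds ratio 2.5, 30% of patients with long duration, and the long-duration odds ratios below.

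| Odds ratio, long v short | Power without / with duration | SE of log OR without / with | Mean log OR without / with |
|---|---|---|---|
| 0.5 | 66.7% / 70.6% | 0.369 / 0.378 | 0.908 / 0.936 |
| 0.33 | 66.3% / 70.0% | 0.369 / 0.386 | 0.875 / 0.941 |
| 0.2 | 64.3% / 67.7% | 0.371 / 0.398 | 0.842 / 0.946 |

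Power rises by 3 to 4 points. The standard error does not fall; the estimate moves away from the null because it becomes conditional on duration. Simulation error is about 1 point on each power figure: √(0.7 × 0.3 / 1500) = 0.012. A fit in this run also raised a convergence warning.

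**5. Chance imbalance.** Between arms of 69 and 47, the standardized difference in mean duration has SD √(1/69 + 1/47) = 0.19. A difference beyond 0.2 SD occurs about 29% of the time, and beyond 0.4 SD about 3%. With R² of 3 to 10% (correlation 0.17 to 0.32), a typical imbalance of 0.19 SD moves the pain difference by 0.17 × 0.19 × 21.5 = 0.7 to 0.32 × 0.19 × 21.5 = 1.3 points on the 0–100 scale, against the planned 12 for usual care.

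**The case against.** The strongest reply is that the covariate sentence sets only a minimum. Duration may be in the final model, and a condensed article may leave the full list to an analysis plan that is not shown. This stands: no loss of power follows from the text itself, only from leaving duration out. What remains is that the published text fixes four covariates and leaves undecided one the plan already uses elsewhere.

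A second reply is that the size is assumed. This stands too. The 80% resolution figure describes overall course, not prognosis by duration at entry, and a subgroup factor signals interest in effect modification, not explained variance. The calculations also use one time point, while the plan has a repeated-measures model.

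Some stronger readings are tempting but unsupported:

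- *The protocol itself says that duration affects treatment response.* The Randomization procedure section says this might hold for BMI and activity level, both of which are in the named set. For duration it is an inference.
- *Precision is lost, above all for recovery.* In a logistic-type model the standard error of the log odds ratio rises slightly when a prognostic covariate is added. The benefit is in power, and a larger benefit than for pain is not shown.
- *Large imbalances are routine.* Differences of 0.4 SD are rare. Chance imbalance is already reflected in the standard error.
- *The cost-effectiveness ratio is affected.* It is built from differences in costs and in recovery with bootstrapping; nothing says those differences come from the adjusted model.

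**Conclusion.** The point holds as a minor improvement, not as an error in the plan. Duration is a valid pre-randomization covariate, already collected and already a subgroup factor, but it is neither stratified on nor named for adjustment. Omitting it would leave the randomized pain comparison unbiased and the type I error unaffected. The cost is forgone power: for pain, roughly 1 to 4 percentage points on a base of 77% if duration explains 3 to 10% of the remaining variance; more if the association is stronger, and essentially nothing if it is weak. For recovery, 3 to 4 points under the assumed odds ratios, with an estimate that is conditional on the covariate. A firm gain, apart from any assumption about prognostic strength, is that naming the covariate now removes a choice that could otherwise be made after the outcomes are known.

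**What to change.** In Data analysis, add baseline duration of complaints to the named covariates for the pain and function models, as a continuous variable with its scale stated (for example log duration) rather than only the 12-month split. State that the same covariates apply to the recovery model, since that sentence now names none, and that its odds ratio is then conditional on them. If an analysis plan already lists duration, align the two texts.

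The cost is a few words, settled before outcome data are examined. No new measurement, no extra patients and no change to the randomization are needed.

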### Objectives

The primary objective of our study is to examine the effectiveness of custom made insoles by a podiatrist, compared to placebo insoles and compared to usual care in general practice and sports medicine alone in patients with plantar fasciopathy in terms of pain.

The secondary objective of our study is to examine the cost-effectiveness of custom made insoles by a podiatrist, compared to usual care in patients with plantar fasciopathy.

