### Sample size

Based on the RCT of Landorf et al. (2006) [18] –pain score 63.4 (SD 21.5), with a difference in pain score of 10.5 (on a scale of 0–100) – it is estimated that with a power of 80 % and an alpha of 0.05 (two-sided), it is possible to detect an effect size of 0.5 with 10.5 points difference on the pain score between patients with a placebo insole and custom made insole with 63 patients in each study group. In addition, a larger difference is expected between the custom made insole group and the usual care group. With a 12-point difference and identical means and SDs, a total of 44 patients are needed per group. A Bonferroni correction will be performed for the secondary comparisons to the usual care group. Taking a loss to follow-up of 10 % into account, a total of 185 patients with plantar fasciopathy (69 in custom made group, 69 in placebo group and 47 in usual care group) will be included in the trial.

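### The percentile bootstrap interval planned for the cost-effectiveness ratio loses its 95% coverage when the recovery difference may be zero, and no condition is set for that case

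*Protocol article*

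**What the plan says.** The Objectives section names the contrast: "The secondary objective of our study is to examine the cost-effectiveness of custom made insoles by a podiatrist, compared to usual care". The Data analysis section defines the ratio: "Differences in costs and differences in recovery will be included in a cost-effectiveness ratio, which estimates the additional costs to completely recover one patient". Its uncertainty is to be expressed in several ways. The first is an interval: "Confidence intervals for the cost-effectiveness ratio will be calculated with bootstrapping, using the bias-corrected percentile method with 5000 replications". The section then adds "Uncertainty of this ratio will be evaluated by presenting a cost-effectiveness plane and sensitivity analyses will be performed to check the robustness of the results" and "An acceptability curve will also be presented".

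Recovery is the dichotomised 7-point Likert rating (Study outcomes), and cost-effectiveness is assessed at 26 weeks. The Sample size section allocates "69 in custom made group, 69 in placebo group and 47 in usual care group" on the basis of a pain difference. No section gives a recovery rate for any arm, and none says what happens to the ratio interval if the recovery difference is near zero.

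**The concern.** A percentile interval needs replicates that can be put in a meaningful order. A ratio with a denominator near zero does not supply them. As the recovery difference passes through zero, the ratio jumps from one infinity to the other. A negative ratio can mean cheaper and more effective, or dearer and less effective, and a positive ratio is equally ambiguous. Sorting such values places the worst replicates (dearer, less effective) below the favourable ones. Bias correction uses the same ordering, so neither it nor more replications repairs the interval.

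At stake is a reported 95% interval for the secondary objective that may not cover at 95%, and that may disagree with the plane and curve drawn from the same replicates.

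**Working it through.** **Inputs from the protocol article.** Custom insole 69 and usual care 47 randomised, with 10% loss to follow-up (Sample size). Analysed: 69 × 0.9 = 62.1 and 47 × 0.9 = 42.3, taken as 62 and 42.

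**What the plan is sized on.** The stated effect size of 0.5 on pain gives 2 × (1.96 + 0.842)² / 0.5² = 62.8, so 63 per insole arm, as stated. This says nothing about the precision of the recovery difference.

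**Assumptions.** Usual-care recovery p₀ of 30–70% at 26 weeks, and recovery differences d of 5 to 20 points, with p₁ = p₀ + d.

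**Formulas.**
- SE = √[p₁(1−p₁)/62 + p₀(1−p₀)/42]
- Share of replicates with a non-positive denominator, if d is the *observed* difference: Φ(−d/SE)
- Probability that the trial's 95% interval for the recovery difference includes zero, if d is the *true* difference: Φ(1.96 − d/SE) − Φ(−1.96 − d/SE)

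**Worked case, p₀ = 0.40, d = 0.10.** SE = √(0.50 × 0.50/62 + 0.40 × 0.60/42) = √(0.00403 + 0.00571) = 0.0987, a 95% half-width of about 19 points. Share: Φ(−1.013) = 0.156. Probability of including zero: Φ(0.947) − Φ(−2.973) = 0.828 − 0.001 = 0.827.

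**Over p₀ = 30–70%** (SE about 0.08–0.10):

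| Recovery difference | Replicates at or below zero (observed difference) | 95% interval includes zero (true difference) |
|---|---|---|
| 5 points | 29–31% | 91–92% |
| 10 points | 13–16% | 79–83% |
| 15 points | 4–6% | 57–67% |
| 20 points | 1–2% | 30–47% |

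The middle column is conditional on the observed difference, because bootstrap replicates centre on the estimate. Averaged over trials with that *true* difference, the share is Φ(−d/(√2·SE)), or about 36%, 24%, 14% and 7% at p₀ = 0.40.

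**What the interval does in one such result.** Illustration at 63 vs 44, with assumed cost difference 200, cost SD 400, p₀ near 40% and a recovery difference of about 10 points. The estimate is about 2,020 per recovered patient. About 85% of replicates are dearer and more effective, and 14% dearer and less effective. The plain percentile interval runs from about −18,600 to 18,000, and the bias-corrected one from about −2,000 to 114,300. The bias correction moves both limits a long way, because the dearer and less effective replicates are counted as lying below the estimate.

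**Simulated coverage of the nominal 95% bias-corrected interval** (p₀ = 40%, cost difference 200; the range spans cost SDs of 400 and 1500 and repeated runs):

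| True recovery difference | Coverage |
|---|---|
| 5 points | about 0.57–0.73 |
| 10 points | about 0.74–0.82 |
| 15 points | about 0.85–0.90 |
| 20 points | about 0.91–0.93 |
| 30 points | about 0.95–0.96 |

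For comparison, the recovery difference detectable with 80% power at 63 vs 44 is about 27 points. The interval behaves well only for effects of about that size.

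**The case against.** Four points can fairly be made for the plan.

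First, the ratio interval is not the only uncertainty display. A reader might infer that the secondary objective stands or falls with it. The Data analysis section does not support that: the plane and acceptability curve are also planned, and both remain valid when replicates cross zero. The plane would show the spread over quadrants directly. This stands and lowers the severity. It does not make the interval correct.

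Second, the sponsor expects a larger effect against usual care than against placebo (Sample size, Discussion). If the planned pain effect of 12/21.5 = 0.56 SD carried over to recovery on a probit scale, usual-care recovery of 30–60% would give a difference of 19–22 points. Only about 1–2% of replicates would cross zero if that difference were observed. This also stands, but a true 20 points still leaves zero inside the trial's 95% interval in 30–47% of trials.

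Third, a reader might take the 80% resolution within 12 months in the Background as showing that the recovery difference will be small. It does not. That figure describes the overall clinical course over 12 months and in terms of complete resolution. It refers neither to recovery without insoles at 26 weeks nor to a between-arm difference.

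Fourth, a condensed article may leave quadrant handling and the willingness-to-pay range to the full plan. That is fair for those details. The interval method itself, however, is stated here without qualification.

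**Conclusion.** The point holds for the ratio interval alone, at minor to moderate severity. The planned method is unreliable when bootstrap recovery differences straddle zero. Under the assumptions above, this is likely at true differences up to about 15 points and still common at 20. Simulated coverage is below nominal through 20 points and close to 95% only at about 25–30.

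A reader might go further and call the interval meaningless at these arm sizes. The documents do not support that: failure depends on the recovery difference, for which they give no figure, and with a large difference the interval works. All magnitudes rest on assumed recovery rates of 30–70%, and the coverage figures also rest on assumed costs. The fault in ordering ratios across quadrants does not depend on those values.

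**What to change.** From the same 5000 replicates, compute the incremental net benefit, λ × (recovery difference) − (cost difference), with 95% intervals over a pre-set range of willingness to pay λ per recovered patient. Make this, with the plane and acceptability curve, the main statement of uncertainty. Report the ratio as a point estimate in place of the unconditional percentile interval.

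If a ratio interval is still wanted, take the values of λ at which the net-benefit interval includes zero (a Fieller-type or acceptability-curve interval). Allow it to be unbounded, and state how the replicates are spread over the quadrants. Giving the percentile interval only when the recovery difference is significant is not a good substitute: intervals would then appear mainly after large observed effects, with no assured coverage.

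The cost is one changed sentence and a few lines of code on replicates that will exist anyway. A willingness-to-pay range must be fixed in advance, which the acceptability curve needs in any case. In some results no finite ratio interval will be reported.
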